**Fig. 1 Fig1:**
[figure not shown]
Visit schedule of StimTox-CD: SCR = screening visit, EVA = evaluation visit, DBS = DBS surgery, RAN = randomization visit, FU = follow-up visit, icon “syringe” ≙ BoNT or placebo injection, icon “reflex hammer” ≙ clinical assessment, icon “operating room” ≙ DBS surgery, icon “lightning” ≙ DBS setting/sham stimulation

**Table 1 Tab1:** Eligibility criteria

Inclusion criteria	Exclusion criteria
• Suffering from isolated, idiopathic or hereditary cervical dystonia for more than 2 years • Moderate to severe symptom severity of dystonia (TWSTRS total score ≥ 20 points and TWSTRS motor score ≥ 15 points) • Age between 18 and 75 years • Adequate therapy response of BoNT A treatment during test injection procedure (≥ 25% reduction of points in TWSTRS motor score 4 weeks after baseline) • Previous BoNT injection ≥12 weeks before screening visit • Written informed consent to study participation, including patient’s agreement to undergo DBS procedure	▪ Mild dystonic symptoms (TWSTRS total score < 10 points and TWSTRS motor score < 5 points) ▪ Suffering from severe depression with ongoing suicidality (BDI > 25 points) ▪ Mild cognitive impairment (MCI) and dementia (MDRS ≤125 points) ▪ Ongoing acute psychosis ▪ Drug or alcohol abuse ▪ Pregnancy or lactation, women of childbearing age without secure contraception ▪ Illiteracy ▪ Surgical contraindication to DBS ▪ Concurrent participation in other clinical trials ▪ Any medical or psychological condition associated with the risk of insufficient compliance and/or early termination of the study

All participants undergo stereotactic implantation of deep brain electrodes in GPi under general anaesthesia. Comparable to previous dystonia DBS studies, the applied neurostimulation system is ACTIVA PC (MEDTRONIC, Minneapolis, USA), including matching electrodes 3387 and 3389 [13, 19]. DBS procedure depends on local standards in each study centre. There are no detailed specifications on perioperative management and stereotactic procedure. Only a preoperative MRI-scan (including T1-, T2, gadolinium-enhanced and inversion recovery sequences) in general anaesthesia and a postoperative image control of electrode positioning are mandatory.

6 (±1) weeks after DBS implantation patients are divided in two study arms during “randomization visit” (RAN). Table 2 is showing the full data set, which is collected at RAN as baseline for the upcoming blinded study phase. Neurostimulation will be now activated for the first time and acute stimulation effects and adverse effects of all electrodes are tested in a structured fashion (“monopolar review”). In DBS group a local DBS expert implements an effective stimulation setting concerning stimulation amplitude and choice of electrodes after “best clinical practice” and a predetermined algorithm. Frequency must be adjusted to 130 Hz, pulse duration to 90 μs. In BoNT group stimulation amplitude is set to 0 V. This group is injected with BoNT by an experienced physician. The decision on preferred drugs (Onabotulinumtoxin A: BOTOX, Abobotulinumtoxin A: DYSPORT or Incobotulinumtoxin A: XEOMIN), applied dosage and injection technique (number of injections, injection site or guiding-techniques) is up to the discretion of the treating physician and supposed to correspond to best clinical practice. During the same visit, patients in DBS group get also injected, but only with saline. Neither patient nor treating physician is informed about the allocation to the study group, in the sense of a double-blind trial design. Obviously DBS setting is not appropriate to be implemented in a blind manner, what causes the need of two separate teams of physicians at each study site; one blinded (or BoNT) and one unblinded (or DBS) team.

**Table 2 Tab2:** Synopsis of interventions and data sets (displayed for single SimTox-CD study visits)

	Screening visit/SCR	Evaluation visit/EVA	DBS surgery/DBS	Randomization visit/RAN	Follow-up visit 1/FU1	Follow-up visit 2/FU2	Follow-up visit 3/FU3	Follow-up visit 4/FU4	Follow-up visit 5/FU5
timeline (weeks)	−14 (+/−1)	− 10 (+/− 1)	−6 (+/− 1)	0	+4 (+/− 1)	+ 12 (+/− 1)	+ 16 (+/− 1)	+ 24 (+/− 1)	+ 48 (+/− 1)
Interventions									
BoNT test injection	X								
DBS surgery			X						
Testing of stimulation (side) effects				X					
DBS setting/sham stimulation^a^				X		X			
Blind BoNT/placebo injection^a^				X		X			
Unblind neurostimulation								X	X
Randomization				X					
Data set									
Informed consent	X								
Inclusion/exclusion criteria	X	X							
Medical history	X								
Concurrent medication	X				X	X	X	X	X
TWSTRS	X	X		X	X	X	X	X	X
Tsui Rating Scale	X	X		X	X	X	X	X	X
Bain Tremor Rating	X	X		X	X	X	X	X	X
GCI	X	X		X	X	X	X	X	X
CDQ-24	X			X				X	X
SF-36	X			X				X	X
EQ-5D	X			X				X	X
MDRS	X			X				X	(X)
BDI	X			X				X	(X)
BPRS	X			X				X	(X)
Video recording	(X)	(X)		X	(X)	(X)	(X)	X	X
Questionnaire on DBS procedure			X						
Postoperative control of electrode position				X					
AE					X	X	X	X	X
DBS settings				X	X	X	X	X	X

^a^according to randomized group allocation

Abbreviations (in alphabetical order): *AE* adverse events, *BoNT* Botulinum neurotoxin, *BDI* Beck Depression Inventory, *BPRS* Brief Psychiatric Rating Scale, *CDQ*-24 Craniocervical Dystonia Questionnaire, *DBS* deep brain stimulation, *EQ-5D* Euroquol (life quality questionnaire), *GCI* Global Clinical Impression Scale, *MDRS* Mattis Dementia Rating Scale, *TWSTRS* Toronto Western Spasmodic Torticollis Rating Scale, *SF*-36 Short Form 36 (life quality questionnaire)

4 (±1) weeks after randomization first follow-up visit (FU1) is scheduled. Clinical outcome parameters are evaluated by blinded physicians. The same procedure is repeated during FU2 and FU3 (12 (±1) and 16 (±1) weeks after RAN), with a second blindly applied BoNT or placebo injection. In FU2 also adjustments of DBS settings are allowed to improve neurostimulation effect in DBS group. The blinded study phase ends in FU4, 24 (±1) weeks after randomization. Neurostimulation is now activated also in BoNT group and the open trial phase starts. Up from FU4, patients are treated commonly without restrictions concerning DBS programming or BoNT injection, treatment must basically conform again to best clinical practice. During FU5, after another interval of 24 (±1) weeks, study ends and a last detailed clinical assessment is intended.

## Outcome measures

The primary outcome parameter is the difference in TWSTRS total score 6 month after implantation. We hypothesize that under optimized treatment in both groups there should be no discrepancy in symptom severity at FU3 (4 weeks after injection of BoNT at the time of medication’s peak effect).

We defined changes in TWSTRS motor score, TSUI score, CDQ-24 and SF-36 to serve as secondary outcome parameters. Additionally, we measure frequency and severity of spontaneously reported AE in both treatment arms.

Additionally, we will describe the difference in TWSTRS total score between patients of DBS group at FU4 and BoNT group at FU5. At both time points, patients are treated with effective neurostimulation for 6 months, respectively. We suppose the same therapy response of effective DBS in both arms, regardless if the stimulation is applied in a blinded or unblinded fashion.

As other hypothesis we will investigate if the maximum treatment effect of DBS is achieved 6 month after activation. Therefore, we will quantify variations in TSWTRS score in the DBS group 6 and 12 months after randomization.

Motor symptom severity is basically evaluated by using standardized and well-established scales like TWSTRS motor and Tsui score. Tsui includes also a tremor item, which is missing in TWSTRS. Dystonic head tremor is also assessed by the Bain Tremor Rating Scale. Additionally, the severity of dystonia is ranked by patients and physicians using a numeric rating scale (1–10) as element of the Global Clinical Impression (GCI) scale.

Questionnaires referring to pain and disability are also part of TWSTRS total score. Another dystonia-specific tool applied to assess quality of life of patients suffering from cervical dystonia is the Craniocervical Dystonia Questionnaire (CDQ-24). Two further standardized forms supposed to measure general health-related quality of life were chosen to be completed by study participants: SF-36 (Short Form 36) and EQ-5D (Euroquol). To exclude relevant cognitive deficits Mattis Dementia Rating Scale (MDRS) will be applied. Depressive symptoms are assessed by Beck Depression Inventory (BDI). For other psychiatric comorbidities we screen by using the Brief Psychiatric Rating Scale (BPRS).

All scales and questionnaires are used in their German version.

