**Methods:**

We aim to recruit 66 cervical dystonia patients into a double-blind comparison of pallidal neurostimulation versus botulinum neurotoxin type A. Eligible patients need ≥25% motor symptom reduction 4 weeks after a neurotoxin test injection, but are willing to undergo DBS surgery due to unsatisfactory symptom control. All participants will be implanted with a DBS system, and randomized into 2 groups: First group will receive effective neurostimulation and saline injections into dystonic muscles. Second group is treated with regular neurotoxin injections and undergoes a sham-stimulation. Primary outcome is the change in TWSTRS total score between baseline and 6 months of therapy. Secondary outcome parameters are corresponding changes in TWSTRS motor score, Tsui score, CDQ-24 and SF-36. Safety will be assessed by frequency and severity of reported adverse events. Statistical analysis includes intention-to-treat and per protocol populations, analysis based on imputation of missing values and analysis adjusting for differences in baseline TWSTRS. After 6 months of blinded treatment all patients will receive open-label neurostimulation and neurotoxin treatment as needed, and are followed up 48 weeks after randomization.

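### Two descriptive follow-up comparisons are read as showing the DBS response, but each uses one FU5 measurement that may include toxin and free reprogramming

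*Protocol article*

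**What the plan says.** Protocol article, Outcome measures, plans two comparisons beyond the primary and secondary outcomes.

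- **Comparison 1** is between arms: "we will describe the difference in TWSTRS total score between patients of DBS group at FU4 and BoNT group at FU5". Its premise is that "At both time points, patients are treated with effective neurostimulation for 6 months, respectively", and its expected reading is: "We suppose the same therapy response of effective DBS in both arms, regardless if the stimulation is applied in a blinded or unblinded fashion". Blinding is the only difference named.
- **Comparison 2** is within the DBS group: "we will quantify variations in TSWTRS score in the DBS group 6 and 12 months after randomization". Its purpose is stated as "we will investigate if the maximum treatment effect of DBS is achieved 6 month after activation".

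The treatment rules are given elsewhere. Under Study protocol, the DBS group's blinded injections are saline, and the settings at the randomization visit are constrained ("Frequency must be adjusted to 130 Hz", with a pulse duration of 90 μs). Adjustment is allowed at FU2. The Blinding section adds an amplitude rule tied to the adverse-effect threshold. From FU4, according to the text after Table 2, "patients are treated commonly without restrictions concerning DBS programming or BoNT injection". The Abstract (Methods) agrees: "all patients will receive open-label neurostimulation and neurotoxin treatment as needed".

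**The concern.** The premise of comparison 1 matches the arms on months of stimulation and stops there. The two measurements also differ in access to toxin and in freedom of programming. Comparison 2 has the same gap between its two time points.

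This matters because every participant had to show at least a 25% motor-score reduction after a toxin test injection, so any toxin given in the open phase goes to known responders. In comparison 1, similar scores could reflect a weaker DBS response topped up by toxin. In comparison 2, an improvement by month 12 could come from toxin or reprogramming rather than from DBS still building up, and stable scores could hide a waning DBS effect. Neither result would answer the question as worded.

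**Working it through.** **Plan's own figures.** The article states no figure for these two comparisons. The primary sample size, which supplies the inputs below, reproduces:
- Pooled SD = √((15.2² + 11.7²)/2) = 13.56.
- Standardized difference = (23.1 − 11.0)/13.56 = 0.892 (stated as 0.90).
- With 28 per arm and a two-sided level of 0.05, noncentral-t power is 90.6%.
- 28/0.85 = 32.9, so 33 per arm and 66 in total, as stated.

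**Treatment state at each measurement** (Study protocol, Table 2, Blinding)

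| Measurement | Used in | Injections | Programming | Weeks since surgery |
|---|---|---|---|---|
| DBS group, FU4 | 1 and 2 | Saline at weeks 0 and 12; last scheduled toxin is the screening test injection, 14 + 24 = 38 weeks earlier | Protocol-set, adjustment at FU2 | 6 + 24 = 30 |
| BoNT group, FU5 | 1 | Toxin as needed after FU4 | Unrestricted | 6 + 48 = 54 |
| DBS group, FU5 | 2 | Toxin as needed after FU4 | Unrestricted | 54 |

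One side of each comparison is affected. The open phase lasts 24 weeks, longer than the 8 to 16 week reinjection interval given in the Background, so there is time for toxin to be given before FU5. The text shown states no toxin-free interval before FU5.

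**Illustrative size of the toxin part.** Bias ≈ (share injected) × (toxin effect added to DBS at FU5). The article gives neither quantity, so both are assumed. The added effect is set at 25%, 50% and 100% of the cited 11.0-point peak effect.

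| Share injected | 2.75 points | 5.5 points | 11.0 points |
|---|---|---|---|
| 25% | 0.69 | 1.38 | 2.75 |
| 50% | 1.38 | 2.75 | 5.50 |

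The direction is towards lower (better) FU5 scores. The effect of free reprogramming comes on top and cannot be quantified from the article.

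**Precision of comparison 1.** Both groups are on DBS, so the DBS SD of 15.2 is used. It is an SD of change, and stands in for the unknown SD of the scores.
- SE = 15.2 × √(2/28) = 4.06.
- 95% half-width = t(0.975, 54) × 4.06 = 8.14 points.

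**Precision of comparison 2.** This comparison is paired. With 28 patients, SD 15.2 and an assumed correlation ρ, the half-width is t(0.975, 27) × 15.2 × √(2(1 − ρ))/√28. That is about 5.9 points at ρ = 0.5 and 3.7 at ρ = 0.8, so a given bias weighs more here than in comparison 1.

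**The case against.** The strongest reply is that the stakes are low. Neither comparison is the primary outcome or a listed secondary one, and the verbs are describe and quantify. The Abstract is open about toxin in the open phase, Table 2 already records concurrent medication and DBS settings at FU4 and FU5, and detailed handling of toxin use belongs in the full protocol or SAP. All of this stands. It lowers the weight of the point and shortens the fix. It does not remove the point, which concerns a stated premise and a stated reading that conflict with the treatment rules in the same article, not an omitted analysis.

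Several stronger readings are tempting but unsupported:

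- **That both sides of comparison 1 are contaminated.** The DBS group is taken at FU4, before any open-label toxin.
- **That the bias could reach 8.3 points and exceed the interval.** That needs 0.75 × 11.0, meaning three quarters of patients injected, all at the full peak effect cited for about 4 weeks after injection, and fully additive to DBS. Nothing in the article supports that combination.
- **That a later gain will be credited to slow-building stimulation.** The article does not say so; the wording merely permits it.
- **That scores after toxin should be set missing and imputed.** FU5 is the only visit after FU4. At a 75% share, 21 of 28 scores would be imputed from 7 patients who, with toxin given as needed, are plausibly the better DBS responders.
- **That comparison 1 must use change from FU4 in the BoNT group.** Scores in randomized arms, stratified on baseline TWSTRS, can be compared directly. An FU4 baseline in one arm only is post-randomization and shaped by toxin.

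**Conclusion.** The concern holds as a matter of interpretation. As written, neither comparison isolates DBS, because each sets a saline-only FU4 measurement under protocol-set programming against an FU5 measurement that may include toxin and free reprogramming. Blinding is not the only difference in comparison 1.

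The size of the bias cannot be determined from the article. The range of about 0.7 to 5.5 points rests on assumed shares of 25% to 50% and assumed added effects of 2.75 to 11 points. It lies below the half-width of about 8.1 points for comparison 1, so the bias may be small or material.

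A reader might infer that the trial's main result is compromised. It is not: the primary comparison ends at FU4, before the open phase, and the sample size is unaffected. What is at risk is a statement about the durability, or the equality across arms, of the response to DBS alone.

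**What to change.** 1. Reword Outcome measures so that FU5 results are described as open-label DBS with toxin as needed, name toxin and programming alongside blinding as differences in comparison 1, and drop the inference to DBS alone in both comparisons.
2. Report by arm the share given toxin after FU4, the time from last injection to FU5, and programming changes between FU4 and FU5. Use the concurrent-medication and DBS-settings records already planned, and make sure that toxin injections and their dates are captured there.
3. Add a descriptive sensitivity analysis by toxin exposure between FU4 and FU5, with the caveat that patients not given toxin are likely the better DBS responders, so that subset does not estimate the effect of DBS alone either.

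The cost is a change of wording, a check on one existing data field, one extra descriptive analysis and a weaker claim about DBS durability. Open-label care does not change.

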### Randomization

Patients are allocated in a 1:1 ratio into the two study arms by stratified block randomization. Randomization procedure is operated centrally via GCP-compliant EDC system. The categorized baseline TWSTRS total score serves as single stratification factor to aim approximately equal distribution of symptom severity in both groups.

### Statistics

Sample size calculation is based on primary outcome parameter TWSTRS total score change from baseline to FU4. The primary statistical analysis consists in a mean value comparison of the primary outcome between both treatment groups by the independent two-sample T-Test. For sample size calculation we refer to data from previously published studies. A GPi-DBS trial showed a mean therapy effect in TWSTRS total score in patients undergoing neurostimulation of minus 23.1 (±15.2 SD) points [19]. A mean maximum effect of neurotoxin treatment is described with minus 11.0 (±11.7 SD) points on TWSTRS total score at an average of 4 weeks after injection [6]. The resulting standardized mean difference of TWSTRS scores between both groups is 0.90. Using these assumptions a sample size of 2 × 28 = 56 patients ensures a power of 90% to detect this effect size as significant (at significance level 0.05) deviation from the null hypothesis (no difference between mean TWSTRS change scores in DBS and BoNT group). Taking into account a drop-out rate of 15% (conservative estimation) 2 × 33 = 66 must be randomized. Furthermore we assume that 20% of patients will refuse informed consent to undergo DBS after screening and another 20% will fail inclusion criteria of sufficient botulinum treatment response after test injection. Consequently, a total number of 2 × 52 = 104 patients will have to be screened to reach the calculated sample size.

Group comparisons for target variables with sample distributions compatible with the assumption of normality will be conducted by using the two-sided independent sample Student’s T-Test or the paired sample T-Test for within group comparisons (changes between visits). For variables with sample distributions not compatible with the assumption of normality non-parametric tests like Mann-Whitney-Test, Wilcoxon Signed Rank Test or Friedmann Test will be applied. Effects will be considered significant if *p* < 0.05.

The primary statistical analysis of the primary outcome parameter as well as the secondary outcome parameter change in TWSTRS motor score, TSUI score and SF-36 score will be based on the intention-to-treat (ITT) population. To proof robustness of results two further analyses of sensitivity will be performed: the first one refers to all randomized patients with imputation of missing values after 6 months by appropriate methods of missing-data imputation depending on which missing-data mechanism could be reasonable. The second method includes only patients of per protocol (PP) population.

To address the question how much TWSTRS total score values differ between DBS and BoNT group on average, when patients would be start at baseline with the same score values, we will use ANCOVA (target variable: TWSTRS total change score from baseline to 6 months after operation, main factor: treatment method, covariate: baseline TWSTRS). Thereby we will adjust to imbalances in the TWSTRS distributions at baseline and the variance within the groups should be reduced.

Also for secondary outcome parameters an ANCOVA will be applied using treatment group as main factor, adjusted for each baseline variable as covariate. Furthermore longitudinal data of scores will be analysed by using GEE (generalized estimating equation) and linear models (“mixed models”). This will be helpful to describe interindividual variability of therapy response.

Safety analysis contains a structured list of AE of both study groups. Possibility of relation to study’s interventions will be judged by physicians of the unblinded team. Incidence of AE will be assessed by using Fisher’s Exact Test (analysis by patients: comparisons of proportions of patients with at least one corresponding event) and negative binomial regression (analysis by events: comparisons of counts of occurring events).

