## Abstract

**Background:**

Selective peripheral denervation via botulinum neurotoxin injections into dystonic muscles is the first-line treatment for cervical dystonia. Pallidal neurostimulation is a potent alternative, but currently restricted to patients failing on neurotoxin therapy. As botulinum neurotoxin is partially effective but often unsatisfactory in a relevant proportion of patients, earlier neurostimulation might be advantageous in providing stable symptom control and preventing disability. This trial intends to demonstrate, that pallidal neurostimulation is superior to neurotoxin injections in best clinical practice for controlling the symptoms of cervical dystonia and that it is safe in patients with a partial therapy response to peripheral denervation. We hypothesize a better outcome in everyday functioning and health-related quality of life of neurostimulated patients.

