Chemical denervation via injection of botulinum neurotoxin (BoNT) into dystonic neck muscles is applied as first line treatment of CD; its efficacy and safety has been demonstrated in several randomized controlled trials [5, 18]. BoNT injections are shown to reduce mean symptom severity substantially defined as reduction between 9.7 to 11 points on Toronto Western Torticollis Rating Scale (TWSTRS) [2, 6]. In addition, its application is superior to pharmacological treatment with anticholinergic drugs [3]. As the neurotoxin effect is only temporary, repeated injections are necessary within a period of 8 to 16 weeks. Furthermore, the toxin effect builds up within a period of 1–4 weeks after injection; therefore, CD symptom severity tends to fluctuate during BoNT therapy. Beside these pharmacological response fluctuations, patients may experience a variable benefit from repeated injections, because the treatment is skill-dependent and limited by the reproducibility of applying equivalent toxin dosages into partly deep lying neck muscles. Beyond the principle efficacy established in pivotal trials, few studies have addressed the long-term efficacy and stability of BoNT treatment responses in daily practice. In an observational study Misra et al. reported that more than 60% of CD patients are treated satisfactorily with BoNT; however, considering the criterion of “duration of effect ≥ 12 weeks” reduced this proportion up to 29% [14]. A further limitation of BoNT therapy arises when complex dystonic patterns including tremor or jerky movements appear; in these cases, many muscles are involved in an intricate interplay, which apparently impedes a target-oriented injection. Additionally, dose-dependent adverse events (AE) may limit the treatment, such as neck weakness, dysphagia, dry mouth or dysphonia [7]. During chronic treatment, secondary therapy failure due to BoNT neutralizing antibodies develops in up to 5% of patients [10]. Despite these limitations and the discomfort associated with repeated BoNT injections, many patients adhere to this therapy, because they are not aware of potential alternatives.

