## Methods/design

### Study protocol

Figure 1 shows the study schedule of StimTox-CD. During “screening visit” (SCR) a test BoNT injection is applied to prove partial therapy response of neurotoxin treatment. 4 (±1) weeks later in “evaluation visit” (EVA) treatment effect is quantified by clinical assessment comprising inter alia TWSTRS motor score. Finally, a minimal motor-symptom reduction of 25% is required to fulfil all inclusion criteria. Table 1 shows a comprehensive list of the criteria applied to choose eligible patients for the study.

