### Visit schedule

To provide a fair comparison between the two treatments with time varying efficacy, we took special care in scheduling the study visits. Baseline visit takes place 6 weeks after operation. This interval was chosen to reduce the impact of the surgical stun effect of electrode implantation. Additionally, motor symptom control efficacy is evaluated in FU1 and FU3 (each 4 weeks after BoNT injection), when the neurotoxin treatment effect is supposed to be maximal [6].

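### The sole primary time point, FU4, lies 12 weeks after the last toxin injection, so it supports superiority at the end of an injection interval, not unqualified superiority over best-practice toxin

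*Protocol article*

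**What the plan says.** - **Aim.** The Abstract intends to show that "pallidal neurostimulation is superior to neurotoxin injections in best clinical practice" for symptom control. The end of the Background and the Perspective repeat this without a time qualifier.
- **Primary endpoint.** The Statistics section says: "Sample size calculation is based on primary outcome parameter TWSTRS total score change from baseline to FU4". The primary test is a two-sample t-test on that change. Outcome measures dates the endpoint from implantation instead; I take FU4, the visit used for sizing.
- **Baseline.** The Study protocol section describes the data set "which is collected at RAN as baseline for the upcoming blinded study phase". RAN is week 0. The previous toxin was given at screening, week −14, where "a test BoNT injection is applied to prove partial therapy response of neurotoxin treatment".
- **Injections.** The text after Table 2 describes FU2 and FU3 "with a second blindly applied BoNT or placebo injection". Table 2 marks blinded injections only at RAN and FU2 (week 12), and Outcome measures confirms that FU3 is 4 weeks after an injection.
- **End of blinding.** "The blinded study phase ends in FU4, 24 (±1) weeks after randomization".
- **Course of the toxin effect.** Background: "As the neurotoxin effect is only temporary, repeated injections are necessary within a period of 8 to 16 weeks". The Visit schedule section places the maximum at FU1 and FU3, each 4 weeks after an injection.
- **Fairness.** The Visit schedule section says: "To provide a fair comparison between the two treatments with time varying efficacy, we took special care in scheduling the study visits". The visits it cites for this are the 6-week post-operative baseline, FU1 and FU3.
- **Expectation at peak.** Outcome measures hypothesizes no discrepancy between optimally treated arms at FU3.
- **Quality of life.** In the blinded phase Table 2 lists CDQ-24 and SF-36 only at RAN and FU4.

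**The concern.** Stimulation is continuous; toxin works in cycles. With a single primary time point, the place of that point within the cycle decides which toxin effect DBS is compared with. FU4 is at the end of the second cycle. The visits that the protocol offers as evidence of a fair comparison, FU1 and FU3, do not enter the primary test.

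At stake is how far the conclusion reaches. The protocol expects the arms to be equal at the toxin's peak, tests superiority 12 weeks after the last injection, and words its aim as superiority in symptom control generally. A significant FU4 difference could come from a real overall advantage of DBS, from toxin wearing off within the interval, or from both. The primary result cannot separate these. For TWSTRS, the FU3 data needed to separate them will exist. For CDQ-24 and SF-36 there is no blinded value near the peak, so no later analysis can supply one.

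**Working it through.** **1. The plan's own figure.** Inputs from Statistics: DBS change −23.1 (SD 15.2); toxin change −11.0 (SD 11.7), described as the mean maximum effect at about 4 weeks; two-sided alpha 0.05; power 90%.

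- Difference: 23.1 − 11.0 = 12.1.
- Pooled SD: √((15.2² + 11.7²)/2) = 13.56.
- Standardized difference: 12.1/13.56 = 0.89 (0.90 if the two SDs are simply averaged).
- The noncentral t-test needs 28 per arm (power 90.6%). Dropout: 28/0.85 = 32.9, so 33 per arm and 66 in total.

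The stated 56 and 66 reproduce.

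**2. Intervals from Table 2.**

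- Last injection to FU4: 24 − 12 = 12 weeks. With ±1 week at each visit: 23 − 13 = 10 to 25 − 11 = 14.
- Last injection to FU3: 16 − 12 = 4 weeks.
- Test injection to RAN: 0 − (−14) = 14 weeks, the same in both arms.

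The sizing contrast is thus DBS against toxin at 4 weeks; the tested contrast is DBS against toxin at 12 weeks.

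**3. How much timing can add.** The document gives no toxin effect at week 12. Let f be the fraction of the 11.0-point peak effect still present at FU4 (assumption, 0 to 1). Relative to the peak contrast, the FU4 contrast shifts towards DBS by (1 − f) × 11.0 points: 0 at f = 1, 2.75 at 0.75, 5.5 at 0.5, 8.25 at 0.25 and 11.0 at 0.

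**4. If DBS only equalled peak toxin.** This takes the FU3 hypothesis at its word: both effects are 11.0 and the FU3 difference is 0. With 28 per arm and SD 13.56 (assumed to apply at FU4):

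| f | FU4 difference | Chance of a significant FU4 result |
|---|---|---|
| 0.75 | 2.75 | 11% to 12% |
| 0.5 | 5.5 | 32% |
| 0.25 | 8.25 | 61% |
| 0 | 11.0 | 85% |

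In the first row, 11.2% is in favour of DBS and 11.6% counts both directions; in the other rows the two agree to the whole percent.

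**5. Under the planning DBS effect (−23.1).** FU3 difference = 12.1. FU4 difference = 23.1 − 11.0f. Average = (FU3 + FU4)/2.

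| f | FU4 | FU3/FU4 average | Ratio | Power for the average |
|---|---|---|---|---|
| 1 | 12.1 | 12.1 | 1.00 | 90.6% |
| 0.5 | 17.6 | 14.85 | 1.19 | 98.0% |
| 0 | 23.1 | 17.6 | 1.31 | 99.8% |

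Power uses 28 per arm and assumes the same SD, 13.56, for the average.

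**The case against.** **FU4 is a legitimate target.** The Background addresses patients with incomplete control or response fluctuations, and the Abstract argues for stable control. Twelve weeks lies within the cited 8 to 16 weeks. This stands: FU4 is a proper primary endpoint if its result is labelled as end-of-interval control.

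**The peak contrast is available.** TWSTRS is taken at FU1 and FU3, and GEE and mixed models are planned. The analysis plan, which is not shown, may rank secondary analyses. This stands in part. The article gives describing variability of response between patients as the purpose of those models, and it ties the general claim to no contrast other than FU4.

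**Moving the primary endpoint has a price.** DBS settings may be adjusted at FU2, only 4 weeks before FU3, and whether DBS is at its maximum by 6 months is itself an open hypothesis. Video is mandatory at RAN, FU4 and FU5 but only bracketed at FU3. This stands, and is why I do not ask for FU4 to be replaced.

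**Stronger readings that the document does not support.**

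- A reader might infer that a trough-to-trough change score biases the comparison at both ends. The 14-week baseline is common to both randomized arms; only the FU4 timing acts differentially.
- A reader might infer that FU4 doubles the DBS advantage. A factor of two follows automatically once the FU3 difference is set to zero. Under the planning effect the ratio is 1.19 at f = 0.5 and 1.31 at f = 0.
- A reader might take the 29% in the Background as showing that almost no toxin effect is left at week 12. It is a satisfaction proportion under a duration criterion from one observational study, not a mean TWSTRS effect.

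**Conclusion.** The point holds as a limit on the claim. The timing, and the direction of its effect in favour of DBS, follow from the protocol's own schedule and its description of the toxin effect. FU4 alone supports superiority 12 weeks after an injection, not superiority over best-practice toxin across the treatment cycle.

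The size is a range, 0 to 11 points, governed by an assumed f that the document does not give. The chances of significance in the equal-at-peak scenario also rest on SD 13.56 and 28 per arm. They describe what timing could do, not what is expected: the protocol's own planning values imply a 12.1-point advantage for DBS even against peak toxin, which sits uneasily with its hypothesis of no difference at FU3. That tension is a further reason to report the FU3 contrast prominently.

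A reader might infer that the sample size is wrong because it uses the peak toxin effect. It is not: any loss of toxin effect by FU4 enlarges the tested difference, so the choice is conservative for power.

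**What to change.** 1. Keep FU4 as the primary endpoint, and word its conclusion as symptom control at the end of the injection interval wherever the aim is stated.
2. Pre-specify as first key secondary the baseline-adjusted treatment difference averaged over FU3 and FU4, taken from the mixed model already planned, and report the FU3 contrast beside it. Test the average only if FU4 is significant, and make the broader superiority claim conditional on it.
3. Collect CDQ-24 and SF-36 also at FU3.

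**Cost.** Wording in the protocol and analysis plan, and two more questionnaires at an existing visit. No new visits or patients: under the planning effect, 28 per arm gives at least 90.6% power for the average at any f from 0 to 1 (same SD assumed).

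**Downsides.** The claim for DBS becomes narrower or less favourable. The average includes an FU3 value only 4 weeks after a possible DBS adjustment and without mandatory video for central rating. A mean of two visits is also only an approximation to the whole cycle.
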